### Significance

Our project focuses on all Canadian parents with low SES who acquire (direct or mediated) online information about child development, education, health, and well-being. In Canada, 42% of nonelderly adults [16,17] and 15% of children live in low-income households [86]. In Quebec, 36% of parents report living in poverty [87]. The demand for information is very high, resulting in frequent internet searches; for example, parents search the internet for child-related information on average 1.3 times per week in Quebec, and 73% of parents report that the internet constitutes their first-line source of parenting information [88].

**Table 1 table1:** Main features of *Naître et grandir* and *AboutKidsHealth*.

Main features	*Naître et grandir* [48]	*AboutKidsHealth* [94]
Website annual traffic	24 million worldwide visits	16.8 million worldwide visits
Information	Developmental, educational, health, and well-being information about children aged under 8 years	Health information about children aged under 19 years
Language	French	English, French, and 10 other languages
Targeted audience	Parents, relatives, and caregivers	Parents, relatives, and caregivers and health professionals

Specifically, our project is important for about half the population of parents of children under 19 years, namely, parents with a low literacy level. Low literacy is a major concern in Canada [16,17,19,20,23]. Results of the 2011 to 2012 survey of a representative sample of 25,267 Canadian parents aged 16 to 65 years showed that 49% of parents have a low literacy level: [89,90] they have difficulty finding, understanding, and using information presented in a dense or lengthy text; navigating complex digital texts; interpreting and evaluating information (constructing meaning); and disregarding irrelevant or inappropriate content when there is competing information (including when correct content is more prominent). Furthermore, our results may help any parent who faces a transitory low literacy level because of a stressful situation. This interdependence between information and emotion is well established in the information literature [91,92].

Our project nevertheless does not focus on the few *information-poor* parents without access (direct or mediated) to online information. In the United States, only 1% of 18- to 29-year olds did not use the internet in 2015 [93]. The Quebec 2015 survey of a representative sample of 23,693 parents of preschool children showed that only 1.5% of parents never know where to find child information [61]. According to information studies, the *information-poor* parents (1) perceive themselves as persons who cannot be helped, (2) adopt self- or group-protective behaviors, (3) are secretive and mistrust others, and (4) consider exposure to information as a risk (harm outweighing benefits) [30].

Our project engages a partnership between N&G and *AboutKidsHealth* (AKH) [94], both popular comprehensive Web-based resources (Table 1). Both resources contain text with a readability level below high school (this level may be higher for disease-related information), visual illustrations, and complementary simple illustrative videos. For each Web page, an audio help system highlights words as they are spoken. In 2016, our librarian did an environmental scan of Canadian parental websites and found multiple specialized resources but only 12 comprehensive resources (including N&G and AKH).

Although this study is a priority in a Canadian context, our results can be important to and applied by all Web editors who provide health information, thereby benefitting all adults with a low literacy level (not only parents). For example, Health Canada policies recommend funding projects that aim to improve access to, and conduct research on, information for Canadians with a low literacy level [23]. Information systems are key components of health systems and crucial to meet human rights and the democratic right to know and communicate [31,95-100]. Among adults, the most frequent searches for information are about health [101]. The demand for high-quality low-literacy health information is, hence, very high.

## Methods

### Organizational Participatory Research Approach

Our project uses an organizational participatory research (OPR) approach. OPR is a form of integrated knowledge translation that blends action research and organizational learning to undertake research with organizations and improve practice [102-107]. N&G (organization) proposed the research questions and will participate in all research steps. The NPI has OPR experience and expertise. The NPI led a CIHR-funded systematic review on OPR key processes and outcomes [107]. A steering committee composed of the NPI, the coprincipal investigator, the partner (principal knowledge user), another knowledge user (AKH), and 2 low-SES parents will meet before and after each phase for planning and interpreting results, respectively. All team members will be consulted and have the opportunity to influence the steering committee’s decision making.

### Methodology and Methods

A mixed-methods multiphase design will be used [108,109]. Ethical approval has been recently obtained from the institutional review board (IRB) of the Faculty of Medicine at McGill University (IRB#A10-E69-17B). Phases 1, 3, and 4 will be informed by our theoretical model (Figure 2).

#### Phase 1 (Objective 1): Identify Barriers and Facilitators to Use Naître et Grandir and Interact With Editors Via Information Assessment Method

##### Design

We will conduct an exploratory qualitative interpretive study to have a better understanding of barriers and facilitators in using N&G and interacting with editors via IAM [110]. Qualitative research is appropriate as it provides in-depth descriptions from the stakeholders’ viewpoint and helps researchers to understand their constitutive elements and variants [111].

##### Setting and Participants

Participants will be 20 users and 20 nonusers of IAM and N&G (additional participants will be recruited to achieve data saturation). First, users will be recruited among low-SES parents who indicate that they agree to be contacted when they complete an IAM questionnaire on N&G and who have used N&G and IAM at least once. N&G will send the group an invitation to participate in a research project via an email containing the research team’s full identification and contact information. The research team will only communicate with N&G users who responded with an interest to participate in the research project via email or phone. Eligible parents will have no high school diploma and have an annual family income lower than Can $40,000 (Quebec poverty line). Second, nonusers (10 who never used the IAM and 10 who never used N&G) will be recruited by a principal investigator (CL) and a collaborator (GD, N&G Director) who work with community organizations for parents with low SES.

##### Data Collection

A research assistant having experience in qualitative interviews with low-SES persons will conduct individual 60-min semistructured face-to-face interviews at the location of each participant’s choice. In line with sociological and information studies [112,113], interviews will explore how participants experience, conceptualize, perceive, and understand aspects of N&G information and the IAM. The interview guide will consist of open-ended questions addressing the participants’ routines in terms of internet use (both for their personal and children’s development information needs), their experience in the use of IAM and N&G’s information, the facilitating aspects of N&G and IAM, perceived barriers in their experience, and suggestions to improve the N&G website and IAM. On the basis of the theoretical model, the interview guide will be developed in a simplified language with input from team members and the steering committee. We will conduct 2 pilot interviews to ensure the questions are comprehensible for the participants. The recruited respondents will receive Can $20 as compensation for their time. In addition to the research assistant’s observation notes, interviews will be audio recorded and transcribed verbatim.

##### Data Analysis

Two principal investigators (PP and CL) have experience in qualitative research and 1 (CL) has experience in qualitative research with populations in situations of vulnerability. With the research assistant and a research trainee, they will read notes and interviews and meet regularly to build memos (meeting minutes with arguments for and against each analytical decision, as rigor is mainly based on researchers’ reflexivity in this design [110]), case summaries, and themes (definitions and key examples) using hybrid deductive-inductive thematic analysis [114,115]. The research assistant will manage the analysis using specialized software (NVivo11). Themes will be derived from our theoretical model (Figure 2; deductive coding) and emerge from the data (inductive coding). Major themes will be barriers and facilitators. For each type of participant (user/nonuser), additional parents will be recruited up to saturation (no new parents’ views of barrier or facilitator). Then, we will harmonize themes [116]. For each theme and definition, we will identify terms, confirm the usage of these terms in reference documents, distinguish correct from incorrect usage, and retain terms that facilitate unambiguous communication. This will lead us to classify, group, and clarify barriers and facilitators in a coherent taxonomy, which will be reviewed by team members and the steering committee. Findings will provide recommendations for improving IAM and N&G.

#### Phase 2 (Objective 2): Improve Naître et Grandir and Information Assessment Method

Two team members (FL and GD) are head directors of the N&G website and will lead this phase. Phase 1 findings will inform the production and implementation of IAM+N&G+ (user-centered design). This version will integrate the perspectives of low-SES parents, the steering committee, research team members, and N&G staff on how to overcome barriers and optimize facilitators. Production of this version will be planned with 2 Web editors and 2 Web engineers from the N&G team. According to Web engineers, 6 months is an ample time frame for production and beta testing. All necessary resources at N&G will be made available to implement IAM+N&G+. Two half-day meetings with principal investigators and N&G staff have been deemed sufficient to plan changes with editors and engineers. The N&G Director stated that she will implement what will be requested by the phase 1 participants, as her mandate (N&G mission) is to specifically address information needs of parents with low SES. For their part, AKH will redesign their website, integrate phase 1 results in this study, and implement IAM+.

#### Phase 3 (Objective 3): Evaluate Use of Information Assessment Method+ Naître et Grandir+, Information Use, and Benefits

##### Design

We will conduct a quantitative prospective longitudinal study to evaluate the impact of the intervention (IAM+N&G+).

##### Setting

Weekly numbers of N&G sessions and IAM ratings will be monitored over 2 years. A session starts when someone opens a Web page and ends when the person (or a relative with the same IP address) does not use the website for more than 30 min. For each quintile of SES, data will be collected for 9 months preimplementation (IAM/N&G) and 9 months postimplementation (IAM+N&G+). To avoid bias related to the *novelty effect*, data collected in the 3 months immediately following the implementation will be excluded from the analysis. The chosen periods also ensure seasonal comparability of the collected outcome data (before and after intervention).

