##### Statistical Analysis

Linear mixed modeling will integrate spatial analytics (geomatics) and account for the clustered nature of the data. The pre/post status, the SES quintile of deprivation, and potentially confounding variables will be included as fixed-effects covariates. The inference model will incorporate random effect terms for individual variables and Web page–specific variables. For each outcome, an interaction term of the SES quintile of deprivation and the pre/post status will be included to assess the pre/post change for each quintile. Estimated regression coefficients and variance parameters will be reported along with appropriate confidence intervals.

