### Timeline and Potential Challenges

Overall, 3 years will be needed to complete this project (Figure 3). Our phases are simple and well defined, and our planning is realistic. In phases 1 and 4, we anticipate no recruitment difficulties. Many parents have already agreed to be contacted for research, and N&G will facilitate the recruitment. Phase 2 is feasible, and the deliverables are realistic given that N&G has already implemented IAM, McGill and N&G have a strong OPR partnership, and N&G is committed to implementing IAM+N&G+. In phase 3, the large number of N&G readers guarantee a large sample. To control for potential seasonal variation in the number of sessions pre- and postimplementation, monitoring will be conducted during the same seasons. To control for contextual changes, variables such as type of device, age, gender, and location are covariates. We have opted for a prospective longitudinal study as monitoring is embedded in N&G routines. In addition, although randomization would provide a higher level of evidence, it was considered unethical to randomly assign low-SES parents to N&G+ or N&G information and impractical for such a popular website (contamination bias) [159]. Moreover, 3 typical potential sources of biases in longitudinal designs may not affect our study: the use of proportions will control for historical events, there will be no *respondent fatigue* as our 2-year pilot data showed that the monthly number of IAM raters is stable, and the social desirability bias will affect pre- and postimplementation periods in a similar manner.

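### Phase 3 lets time enter only as pre/post status across windows a year apart, so a year of background trend falls into each quintile's estimated change

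*Protocol article*

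**What the plan says.** All references are to the protocol article.

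- **Phase 3, Setting.** The series is weekly: "Weekly numbers of N&G sessions and IAM ratings will be monitored over 2 years". For each SES quintile, "data will be collected for 9 months preimplementation (IAM/N&G) and 9 months postimplementation (IAM+N&G". To avoid a novelty effect, "data collected in the 3 months immediately following the implementation will be excluded from the analysis". The section adds: "The chosen periods also ensure seasonal comparability of the collected outcome data (before and after intervention".
- **Phase 3, Statistical Analysis.** "The pre/post status, the SES quintile of deprivation, and potentially confounding variables will be included as fixed-effects covariates". Every outcome gets the same interaction: "an interaction term of the SES quintile of deprivation and the pre/post status will be included to assess the pre/post change for each quintile". On random effects: "The inference model will incorporate random effect terms for individual variables", and also for variables specific to the Web page. The section says clustering will be accounted for. It names no calendar-time term and no effect for week.
- **Timeline and Potential Challenges.** On season: "monitoring will be conducted during the same seasons". Contextual change is left to covariates (device, age, gender, location). Historical events are said to be controlled because proportions are used. The monthly number of IAM raters is described as stable over the 2-year pilot. Randomization was considered and rejected.
- **Table 2.** Outcomes A1 (sessions) and A3 (IAM ratings) are weekly numbers. A2, B1, B2 and C are weekly proportions.
- **Phase 3, Anticipated Results.** All outcomes are expected to increase.

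**The concern.** Matching the windows by season removes seasonal differences. It does so by comparing each post week with the same week one year earlier. With time coded only as before or after, and with no untreated comparison series, whatever changed over that year is credited to IAM+N&G+ unless a covariate explains it. Device, age, gender and location describe who is using the site. They do not capture a general rise or fall in use.

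The predicted result is an increase in every outcome, so ordinary growth in traffic would look like success. The article also goes further than leaving the point open: it states that history may not bias the study, on a ground that does not apply to two of its six outcomes.

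**Working it through.** **1. Offset of the windows.** Inputs are the 9, 3 and 9 months in Setting, with the pre window assumed to end at launch (the timeline figure is not available). Pre runs from month −9 to 0 and post from month 3 to 12. Start to start: 3 − (−9) = 12 months. Midpoint to midpoint: 7.5 − (−4.5) = 12 months. The span is 12 − (−9) = 21 of the 24 monitored months. This agrees with the stated aim of seasonal comparability.

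**2. Bias in the pre/post coefficient.** Take 39 pre weeks (0 to 38) and 39 post weeks (52 to 90). With a linear trend of b per week and no true effect, the pre/post coefficient is b × 52. An assumed 5% a year (b = 0.05/52) gives 0.05, a spurious change of 5%.

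**3. How often this would be called an effect.** The growth and noise figures are assumptions.
- Weekly analysis, noise SD 8%, independent weeks: SE = 0.08 × √(2/39) = 0.0181, and 0.05/0.0181 = 2.76. Two-sided 5% significance is reached in about 78% of runs, or about 76% if growth is taken as log(1.05). With 10% growth it is over 99%.
- Sessions treated as independent counts, at the 5 million per period given in Study Size: z = log(1.01)/√(2/5,000,000) = 15.7 for growth of only 1% a year.
- Ratings at 15,000 per period: 5% growth gives z = log(1.05)/√(2/15,000) = 4.2. For one quintile (3,000 per period, equal split assumed) z = 1.9.
- Outcome C at the pilot rate of 65.4%: a drift of 2 percentage points a year is declared an effect with probability 96% overall (15,000 per period) and 37% in one quintile (3,000). So proportions are not immune.

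**4. Can a trend be fitted in the planned windows?** SEs are in units of the weekly SD, for one series with independent errors.

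| Model on 39 + 39 weeks | Rank / columns | SE of post effect |
|---|---|---|
| Post only | 2 / 2 | √(2/39) = 0.226 |
| Linear trend + post | 3 / 3 | 0.570 (2.5 times) |
| One annual harmonic + trend + post | 5 / 5 | 1.71 (7.6 times) |
| 39 week-of-year dummies + trend + post | 40 / 41 | not estimable |

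**5. What earlier weeks add** (52 week-of-year dummies, trend and post: 54 columns, rank 54).
- 156 contiguous earlier weeks: SE 0.246, and 0.246/0.226 = 1.08 to 1.09.
- Only the 104 pilot weeks, with a gap of 1 to 2 years before the pre window (assumed): SE 0.268 to 0.258, ratio about 1.14 to 1.19.

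**6. Between-quintile contrasts.** A trend common to all quintiles cancels on the scale of the model. On a linear scale, common percentage growth does not: with illustrative weekly counts of 4,000 and 2,000, growth of 5% adds 200 and 100, a spurious difference of −100. On a log scale it cancels.

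**The case against.** The article is not blind to time. Season is handled by design, contextual change by covariates, and four of the six outcomes are proportions, which growth in site use does not shift mechanically. Objective 3 is itself framed as a proportion of low-SES parents. The pilot showed a stable monthly number of IAM raters, which bears on A3. Every model has a quintile by pre/post interaction, and comparing quintiles cancels a shared trend on the model's scale. No session trend is given, so the bias could be small.

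Much of this stands and limits the point. It does not remove it. A1 and A3 are counts, stability is stated for raters and not for sessions, proportions can drift, and the interaction is described as giving the change for each quintile rather than the difference between quintiles.

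Two stronger readings are tempting, and the documents do not support them:

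- A reader might infer that serial correlation is ignored. The article says clustering is accounted for and is silent on residual structure, which an article may leave to the full analysis plan. All that can be said is that the named random effects do not include week, although pre/post status varies only by week.
- A reader might infer that trend and effect can never be separated in the planned windows. That is so only with a separate term for each week of the year. A linear trend alone is estimable, at about 2.5 times the standard error.

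**Conclusion.** The point holds as a should-fix. In the described model, the pre/post change within each quintile absorbs 12 months of any background trend not explained by the covariates. The article's statement on historical events does not protect the weekly counts A1 and A3 and does not rule out drift in the proportions. An assumed 5% a year becomes a spurious change of about 5%, significant in roughly 75% of runs under 8% weekly noise.

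This rests on the pre window ending at launch, and on growth and noise figures that the documents do not supply. The size of the bias is therefore unknown; the exposure to it follows from the design. Between-quintile contrasts are much less exposed, but they are not the estimate the article describes.

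**What to change.** - Extend the pre-implementation series with the earlier weekly Google Analytics and IAM data, at least the September 2014 to August 2016 pilot.
- Fit a segmented model with seasonal terms (week of year or harmonics), a linear trend by quintile, post, and quintile × post. Use a log scale for A1 and A3.
- Allow for correlation at week level, because pre/post status varies only by week.
- Report the between-quintile contrast beside the within-quintile change.
- Keep the 9-against-9-month comparison as a sensitivity analysis.
- In Timeline and Potential Challenges, limit the statement on historical events: it does not apply to A1 and A3, and it lessens but does not remove the risk for the proportions.

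**Cost.** Retrieval of stored data, more analysis, and a standard error about 8% to 20% larger before autocorrelation. The change assumes that the earlier weekly series can be retrieved, that a deprivation quintile can be assigned to earlier sessions, and that the trend is roughly linear over the longer period. The team should check all three before fixing the model.

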##### Participants

All N&G readers and IAM raters across Canada will participate.

##### Measurement

N&G and McGill already use Google Analytics, an objective and reliable automatic data collection of N&G readers’ demographic characteristics and website use behavior (based on javascript codes in each Web page) [117-120]. IAM raters’ demographic data are collected with a questionnaire (linked to an anonymized identifier). The validated IAM questionnaire [53] collects self-reported information use and subsequent expected health/well-being benefits for parents and their child.

**Table 2 table2:** Types of outcomes monitored weekly.

Type	Outcome	Description and data source
A1	N&G^a^ sessions	Weekly number of unique sessions (Google Analytics)
A2	N&G read	Weekly proportion of sessions with at least 1 page entirely read (Google Analytics)
A3	IAM^b^ ratings	Weekly number of IAM questionnaires submitted
B1	N&G mediated	Weekly proportion of IAM ratings information used for the child of someone else
B2	N&G used	Weekly proportion of IAM ratings information used for oneself and one’s child
C	Expected benefits	Weekly proportion of IAM ratings expected health or well-being benefit for a parent and child, including at least 1 of the following self-perceived benefits (IAM choices of response): improvement of the health or well-being of a child, being less worried, prevention of a problem or the worsening of a problem, handling a problem, and being more confident to decide something with someone else

^a^N&G: *Naître et grandir*.

^b^IAM: Information Assessment Method.

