**Figure 1 figure1:**
[figure not shown]
Social gradient in assessing *Naître et grandir* (N&G) information with Information Assessment Method (IAM). A dot represents the total number of IAM ratings completed by all N&G newsletter subscribers living within the postal code areas of a Canadian centile of Material Deprivation. There is a negative linear relationship as areas with higher deprivation have a lower proportion of newsletter ratings/subscribers. The correlation coefficient is −.42 (*P*<.001).

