### Potential Impact Beyond
*Naître et grandir* and
*AboutKidsHealth*

Results will inform the development of an open access online tool kit on how to adapt websites and IAM+ for a low literacy audience (a growing consideration of many Web editors). The tool kit will be designed to be generalizable to all types of online consumer health information in Canada. It will include guidance with 3 main messages: (1) how to produce simple information in lay language with audio and visual content, (2) how to better interact with low-SES persons using IAM+, and (3) how to use consumers’ IAM+ ratings and feedback to continuously optimize information content. The tool kit will be freely available to any Web editor via the Quebec SPOR-SUPPORT Unit and IAM websites. The NPI has experience in developing tools and leads the method development platform of the Quebec SPOR- SUPPORT Unit.

Our primary knowledge translation goal for knowledge user audiences will be to raise awareness about our main messages and drive attention to the tool kit. A secondary knowledge translation goal will be to support the implementation of the toolkit by Web editors. Knowledge users will disseminate our work in multiple Canadian organizations. As per reviews on scaling up [148-150], we will update our 2016 environmental scan and contact all Canadian websites targeting parents. A specialized librarian (collaborator) will reach additional health websites through librarian listservs and peer networks. Team members will raise general awareness for the tool kit and deliver our main messages to a variety of academic and nonacademic knowledge user audiences via a range of knowledge translation strategies (conference presentations, open access peer-reviewed publications, plain language summaries and grey literature, social media, and networks). Multiple knowledge translation channels will be used including Twitter (@UniteSoutien) and websites such as the Quebec SPOR-SUPPORT Unit and the IAM websites [151,152].

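### Objective 3 is about the proportion of low-SES parents who interact through the IAM, but its only outcome for how often they do so (A3) is a count without a denominator

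*Protocol article*

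**What the plan says.** The Goal and Objectives section words Objective 3 as a proportion, both for engaging with the site and for interacting with editors through the IAM. The Phase 3 Design paragraph sets out to "evaluate the impact of the intervention (IAM+N&G", that is, both new versions together, and the Setting paragraph gives them one shared pre/post contrast.

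In Table 2 (Phase 3, Measurement), site use has a count of sessions (A1) and a per-session proportion (A2). IAM use has A3 only: "Weekly number of IAM questionnaires submitted". B1, B2 and C are proportions among questionnaires already submitted, so they carry no information on how likely a reader is to submit one.

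Three other places bear on the scale of A3:

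- The Figure 1 legend states the pilot gradient per subscriber: "areas with higher deprivation have a lower proportion of newsletter ratings/subscribers".
- Timeline and Potential Challenges argues that working with proportions takes care of historical events.
- The Statistical Analysis paragraph names pre/post status, SES quintile, their interaction and possible confounders. It names no term for session or subscriber volume.

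**The concern.** A count of questionnaires is the product of how many opportunities to rate there were and how often they were taken. Objective 3 and Figure 1 concern the second factor; A3 mixes the two. The Phase 3 Anticipated Results paragraph expects every outcome to rise, sessions included, so the plan itself expects the first factor to move.

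Matching seasons and dropping the first three months after implementation do not remove this, because the extra sessions would be a lasting result of the intervention. Taking the low-SES share of all ratings does not remove it either: if low-SES sessions grow faster than the others, that share grows with them.

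At stake is the second half of Objective 3. A rise in A3 could be reported as a larger proportion of low-SES parents interacting with editors when that proportion is unchanged or lower.

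**Working it through.** **Inputs.** Study Size: about 5 million sessions and 15,000 ratings in each period. Introduction (Rationale): 34,021 pilot ratings in 24 months. Table 3: 8.3 million Canadian visits in 2015. Session growth, the change in rate and the share of ratings from the site are not in the document. They are assumptions, shown as ranges.

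**Step 1, the stated volumes.** Pro rata to nine months, 34,021 × 9/24 = 12,758 ratings (stated 15,000) and 8.3 million × 9/12 = 6.2 million visits (stated about 5 million). The stated values are rounded forecasts and the Canadian pilot counts are not given, so the gap is no evidence of an error. It does not affect the percentages below, which do not depend on the baseline.

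**Step 2, baseline rate.** 15,000 / 5,000,000 = 3.0 ratings per 1,000 sessions, both channels pooled.

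**Step 3, all ratings arising from sessions.** With session change g and rate change d, the A3 ratio is (1 + g) × (1 + d).

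| g | d | Ratings | A3 change | Rate per 1,000 |
|---|---|---|---|---|
| +20% | 0 | 6,000,000 × 0.0030 = 18,000 | +20% | 3.00 |
| +20% | −10% | 6,000,000 × 0.0027 = 16,200 | +8% | 2.70 |
| +10% | −5% | 5,500,000 × 0.00285 = 15,675 | +4.5% | 2.85 |

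**Step 4, how far the rate can fall before A3 falls.** The break-even fall is 1 − 1/(1 + g): 4.8%, 9.1%, 16.7%, 23.1% and 33.3% for session growth of 5%, 10%, 20%, 30% and 50%.

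**Step 5, only part of the ratings arising from sessions.** Let s be that share, with subscriber numbers constant and d the same in both channels. The A3 ratio is then (1 + s × g) × (1 + d). With g = +20% and s = 0.5:

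- d = 0 gives 1.10, so A3 still rises 10% with no change in propensity.
- d = −10% gives 1.10 × 0.90 = 0.99, so the sign no longer reverses.

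For g = +20% and d = −10%, A3 rises only if 0.90 × (1 + 0.20 × s) > 1, that is s > 0.56. The inflation is present at any s above zero; the reversal of sign needs a large s.

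**Step 6, could chance hide it?** Suppose the most deprived quintile gives 10% to 20% of ratings (1,500 to 3,000, assumed). In the second row of the table, a simple Poisson comparison without overdispersion gives z of about +2.1 to +3.0 for the count and −2.9 to −4.2 for the rate. The two measures could each look clear and point in opposite directions. Overdispersion would shrink both.

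**The case against.** Phase 3 evaluates a package. More questionnaires from low-SES readers is a real gain for the editors, even if it comes only from wider reach. A1 and A3 are both followed weekly by quintile, so sessions +20% beside ratings +8% would be visible to an attentive reader, and the ratio can be formed from planned data. An offset is the kind of detail that an article may leave to a fuller document. No figure in the document supports any particular session growth, and newsletter ratings need not follow site sessions at all.

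Much of this stands. A3 is a legitimate measure of feedback volume, the sizes above are illustrations, and the data are adequate. It does not answer the mismatch: Table 2 itself fixes the outcome, as a count, for an objective worded as a proportion.

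A reader might go further and infer that a rise in A3 will be credited to IAM+ alone, so that a worse tool would pass as a success. The document does not say this. Its Design, Objective 3 and Anticipated Results all refer to the two versions together. Nor does the partner site show that an IAM+ result will be used in isolation: under Phase 2, "AKH will redesign their website, integrate phase 1 results in this study, and implement IAM"+, which is again a site change plus the tool, and nothing makes it depend on A3. The tool-kit message "2) how to better interact with low-SES persons using IAM"+ is guidance that no text ties to A3.

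**Conclusion.** The point holds as a mismatch between objective and outcome. A3 cannot show whether a larger proportion of low-SES parents interact through the IAM, and the argument from proportions in Timeline and Potential Challenges does not extend to it. To the extent that ratings arise from site sessions, A3 grows with sessions at an unchanged rate. With all ratings from sessions, an assumed +20% in sessions hides any fall in the rate of up to 16.7%. The size in practice depends on session growth and on the split between site and newsletter ratings, neither of which is given.

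It should not be read as a finding about IAM+ by itself, and a rate would not isolate IAM+ either, because N&G+ may change who visits. Assume that the existing 5 million sessions still rate at 3.0 per 1,000 and that 1 million new casual sessions rate at 1.5. The overall rate is (15,000 + 1,500) / 6,000,000 = 2.75 per 1,000, which is 8.3% lower although no existing reader behaves differently. The weakness lies in the outcome definition, is worth correcting before analysis, and does not undermine the data collection.

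**What to change.** Keep A3 as a measure of volume and add one row to Table 2: a rating rate by SES quintile and week, defined as questionnaires per 1,000 N&G sessions for site ratings and questionnaires per subscriber for newsletter ratings (the Figure 1 measure). It could be fitted, for example, as a count with log sessions or log subscribers as offset, keeping the planned quintile by pre/post interaction. Base the statement on the proportion interacting through the IAM on this rate, reported alongside A1 and A3, and describe it as an effect of IAM+N&G+ together.

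Costs and downsides:

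- A favourable count may look smaller, or vanish, as a rate.
- Sessions and ratings are already planned by quintile, and subscribers by area were available for Figure 1. Each rating must also be identifiable as site or newsletter, and subscriber counts are needed over time; the article does not say whether these are stored.
- A count model departs from the stated linear mixed model for this outcome.
- According to Covariates, quintiles come from reported postal codes for ratings and from geotags for sessions. The per-session rate by quintile therefore carries some misclassification between numerator and denominator. A sensitivity analysis should check this, for instance by applying one area rule to both where the data allow. The per-session rate over all quintiles together is free of this mismatch and can be shown beside it.
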